#### Secondary outcome

2.4.2

##### Spontaneous bowel movements

2.4.2.1

Spontaneous bowel movements refer to bowel movements without using the medication for symptomatic relief of constipation during weeks 3 to 18.

##### CSBM in weeks 11–18

2.4.2.2

This signifies comparing the proportion of participants with CSBM ≥3 between the 2 groups in weeks 11 to 18.

##### BSFS

2.4.2.3

The BSFS has 7 pictures of different styles of stools to facilitate the recording of stool consistency. Each picture had its grade. The first type is the one with the hardest stool, and the seventh type is entirely liquid. It will be recorded in grades per week during weeks 3 to 18. The higher the grade, the harder the stool.^[15]^

##### Straining severity scores

2.4.2.4

The straining severity scores aim to measure the degree of difficulty of defecation during weeks 3 to 18. Straining will be rated with scores of 0, 1, 2, and 3, which indicate “not difficult,” “a little difficult,” “difficult,” and “very difficult,” respectively.

##### PAC-QOL

2.4.2.5

The PAC-QOL contains 28 items to assess the effect of constipation on 4 subscales: physical discomfort, psychosocial discomfort, worries and concerns, and satisfaction. Each item has a score ranging from 0 to 4. A lower score indicates a better quality of life. The PAC-QOL will be assessed at weeks 2, 6, 10, 14, and 18.

##### Medicine use

2.4.2.6

The proportion of participants and the weekly frequency of rescue medication use and other defecation measures will be recorded in the diary.

### Sample size calculation

2.5

In this trial, pass 11 was used to calculate the sample size. There is an absence of studies on acupressure for chronic FC. The selection of the acupoint and the sham acupoint of our study is the same as that of a previous acupuncture study,^[17]^ as is the primary outcome. In this trial, we wanted to achieve 80% power at a significance level of 0.05. Considering a 10% dropout rate, we need 154 subjects in total and 77 subjects per group.

### Randomization and blinding

2.6

The participants will be enrolled in the experimental and control groups at a ratio of 1:1. An independent researcher will generate the randomization sequence using SPSS (SPSS 21.0, SPSS Inc., Chicago, IL). The random numbers will then be placed in opaque envelopes, which will be numbered sequentially and sent to the independent researcher in charge of randomization. The envelopes will be opened sequentially according to the numbers. Then, allocation is determined. The former researcher will unmask the envelopes after interviewing; therefore, the participants and other investigators will be blinded to the allocation. Outcome assessors, data managers, and statisticians will be blinded in this trial and will be separated so that they cannot share information. Furthermore, we will set a standard procedure for communication to ensure treatment blinding. The allocation will be revealed once the trial is completed.

### Safety evaluation

2.7

The participants at home will self-administer acupressure. The participants will be told that if any adverse events (AEs) occur, they should communicate with the researchers at once. Regardless of whether the AE is related to the treatment, the treatment should be terminated when AE occurs. The participants should receive appropriate treatment at once. In 24 hours, the researcher should report the AE to ethical committees that decide whether the participants should drop out of the trial. AEs will also be recorded in a case report form.

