### Intervention

2.3

After randomization, the registered acupuncturist will teach the participants the location of the acupoints and the details of the acupressure manipulation in the first 2-week run-in period. The participants will be provided with pictures, text descriptions, and videos about the acupressure manipulation for further study at home. At the end of the second week, the participants will be asked to go to the clinical trial laboratory to be checked by the registered acupuncturist to manipulate the acupressure accurately. Self-acupressure will be performed twice a day during the intervention period, and the patient should sign in on WeChat every day. If the participant is unable to use WeChat, the print edition of the diary and questionnaires will be provided, and the supervision will be performed by short messages. Participants who do not have 3 or more bowel movements can use 100 mL glycerol or 40 to 60 mL sorbitol anal enema with detailed documentation.

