### Outcome

2.4

Participants will be required to complete a diary of constipation throughout the trial on WeChat. Most outcomes will be extracted from the diary. Moreover, some questionnaires must be completed. If the participant is unable to use WeChat, the print edition of the diary and questionnaires will be provided.

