#### Primary outcome

2.4.1

The primary outcome of this trial is the proportion of participants whose CSBM is ≥3 during weeks 3 to 10 (bowel movements with a sensation of complete evacuation).^[2]^

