### Date analysis

2.9

SPSS (version 21.0; SPSS Inc., Chicago, IL) will be used in statistical analyses by an independent statistician. Continuous variables will be presented as mean ± standard deviation, while categorical variables will be represented as percentages and numbers. The Chi-square test will be used to assess categorical variables, such as the characteristic and demographic data. The *t* test or Wilcoxon rank-sum test will be used for within- and inter-group comparisons according to the homogeneity and normality analysis. The date of the participant receiving at least one treatment will be included in the analysis. Missing data will be dealt with using the worst-case scenario method. We set the confidence interval to 95%. All tests are 2-tailed, and *P*-values <.05 will be considered to be significantly different.

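### Section 2.7 ends acupressure at any adverse event, related or not, with no severity threshold or restart, so harmless events can remove treatment inside the primary outcome window

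*Protocol article*

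**What the plan says.** Section 2.7 (Safety evaluation) asks participants to report any adverse event (AE) at once and then sets the rule: "Regardless of whether the AE is related to the treatment, the treatment should be terminated when AE occurs". The participant is to be treated, and within 24 hours the researcher must "report the AE to ethical committees that decide whether the participants should drop out of the trial". The section gives no grade or seriousness threshold and does not mention restarting acupressure.

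The other sections that bear on this are:

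- Section 2.3 (Intervention): "Self-acupressure will be performed twice a day during the intervention period". Table 1 places that period in weeks 3 to 10.
- Section 2.4.1 (Primary outcome): "The primary outcome of this trial is the proportion of participants whose CSBM is ≥3 during weeks 3 to 10".
- Section 2.9 (Date analysis): "The date of the participant receiving at least one treatment will be included in the analysis" (the first noun is evidently meant to be data).
- Section 2.4 (Outcome): "Participants will be required to complete a diary of constipation throughout the trial on WeChat".
- Section 2.5 (Sample size calculation): "we wanted to achieve 80% power at a significance level of 0.05", and "Considering a 10% dropout rate, we need 154 subjects in total and 77 subjects per group".

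**The concern.** The rule expressly removes the relatedness test, and nothing elsewhere in the article narrows it. A cold in week 4 would end acupressure in the same way as an injury from pressing. The committee's stated decision concerns only whether the person leaves the trial. It comes after treatment has ended and does not give treatment back.

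The treatment weeks and the primary outcome weeks coincide, so every week removed falls inside the window in which response is counted. A stopped participant who stays in the trial remains in the analysis with less than the assigned 8 weeks. That pulls the two arms together. What is at stake is power, not type I error: if AEs occur equally in both arms, the bias is towards no difference.

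The wording also leaves staff unsure whether the stop is permanent or holds only until the committee decides. The two readings cost different amounts.

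**Working it through.** **The plan's own figure.** Section 2.5 gives 77 per group with 10% dropout. 69/0.9 = 76.7, which rounds up to 77, so the plan is consistent with 69 analysable per group at 80% power. (70 × 1.1 = 77 is also possible.) The underlying 69 cannot be reproduced because the article states no response rates. The check therefore works from the planned power.

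**Inputs from the article.** 80% power, two-sided alpha 0.05, 77 per group, 10% dropout, 8 treatment weeks.

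**Assumptions, because the article gives no figure.** A weekly AE probability p of 0.5%, 1% or 2%, equal in both arms; AEs fall mid-week on average; benefit is lost in proportion to treatment weeks lost.

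**Starting power.** The standardised effect at 69 per arm is s = 1.960 + 0.842 = 2.802, which gives 80%. At 77 per arm, s = 2.802 × √(77/69) = 2.960, and power is Φ(2.960 − 1.960) = 84.1%. The first case uses up the dropout allowance and the second uses none of it.

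**Literal reading (no restart).**
- Share stopped by the end of treatment: 1 − (1 − p)^8.
- Mean treated weeks: the average of Σ(1 − p)^k over k = 0 to 7 and over k = 1 to 8.
- Fraction of treatment lost: f = 1 − (mean treated weeks)/8.
- Power: Φ(s(1 − f) − 1.960).

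| p per week | Stopped | Of 154 | Mean weeks | f | Power, 69 per arm | Power, 77 per arm |
|---|---|---|---|---|---|---|
| 0.5% | 3.9% | 6 | 7.842 | 0.0198 | 78.4% | 82.7% |
| 1% | 7.7% | 12 | 7.687 | 0.0391 | 76.8% | 81.2% |
| 2% | 14.9% | 23 | 7.387 | 0.0766 | 73.5% | 78.0% |

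Example at 1% and 69 per arm: 2.802 × (1 − 0.0391) = 2.692, and Φ(2.692 − 1.960) = 76.8%.

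**Break-even with all 77 per arm.** Power is 80% when 2.960(1 − f) = 2.802, so f = 0.0534. That corresponds to p of about 1.4% per week, or 10.5% stopped, about 16 of 154.

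**Pause reading.** Assume each AE costs one week, after which acupressure restarts. Then f = p/(1 + p) = 0.0050, 0.0099 and 0.0196. Power is 79.6%, 79.2% and 78.4% at 69 per arm, and 83.8%, 83.4% and 82.7% at 77 per arm.

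**Cross-check by a different route.** Take 69 per arm and assumed sham response rates of 10%, 20% and 30%. The acupoint rates giving 80% power are then 28.7%, 41.9% and 53.3%. Suppose every stopped acupoint participant responds at the sham rate, however late the stop. Power is 76.0–76.6% if 5% stop, 71.5–72.7% if 10% stop and 61.5–64.1% if 20% stop. The direction is the same. The loss is larger because late stoppers lose all their benefit.

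**The case against.** **The reading.** Section 2.7 describes a sequence: stop, treat, report, committee decision. That fits a temporary safety hold as well as it fits permanent discontinuation. This stands as an ambiguity. It does not rescue the text, because the committee's stated decision is about leaving the trial and no return to acupressure is described. On this reading the loss is 1.6 points at most over the assumed range.

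**A condensed article.** AE grading and restart detail are commonly left to the full protocol. That is fair for those details taken alone. But the article states a stopping rule outright and removes relatedness from it, so the rule itself is open to comment.

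**Size.** No AE rate is given, and with all 77 per arm retained power stays at or above 80% until about 16 participants are stopped. This stands. The 69-per-arm figures also overlap partly with the dropout allowance, if the committee removes some AE cases from the trial. They are better read as the lower end.

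**The dilution model.** Benefit may persist after stopping, and the loss for a responder outcome need not be linear in weeks. This also stands: proportional loss is an assumption, and the cross-check shows a harsher one.

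**Rationale for the present rule.** The teachers of acupressure cannot be blinded (section 3, Discussion). A rule that ignores relatedness treats both arms alike and needs no causality judgement from unblinded staff. This is the best argument for keeping it. It is met by having someone unaware of the arm judge relatedness.

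**Conclusion.** The concern holds as a modest one that is worth fixing. As written, section 2.7 removes treatment for events with no bearing on the safety of a non-invasive, self-applied intervention, and it does so in the weeks that determine the primary outcome.

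In the main calculation, the literal reading costs about 1.5 to 6.5 power points across the assumed AE rates: 80% to 78.4–73.5% at 69 per arm, and 84.1% to 82.7–78.0% at 77 per arm. A one-week pause costs between 0.3 and 1.6 points. These figures rest on assumed AE rates equal in both arms and on benefit lost in proportion to weeks lost. A large power loss has not been shown, and equal rates create no false positive. The reason to act is that the loss is avoidable, the instruction is ambiguous, and the correction is cheap.

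**What to change.** Amend section 2.7 as follows:

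- Permanent stopping is mandatory only for serious AEs, for AEs judged related and above a stated severity, or for events that make acupressure unsafe.
- For all other AEs, acupressure may be paused and restarted, with the dates of both recorded.
- Anyone who stops acupressure continues the diary, the PAC-QOL (constipation quality-of-life questionnaire) and AE follow-up to week 18 unless they withdraw, and stays in the analysis in the arm to which they were randomised. The definition of the analysis set in section 2.9 is a separate question, and this amendment does not depend on it.

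The cost is a wording amendment. The diary already runs throughout the trial and AEs already go into the case report form, so little new data collection is needed. The one downside is that relatedness becomes a judgement. It should be made by a clinician unaware of the arm, not by the acupuncturist who taught the technique.

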### Date collection and management

2.8

Data will be extracted from the diary of constipation and questionnaires. All dates will be recorded in the case report forms (CRFs) stored in the lock-up cabinet. Details of the CRF writing will be formed and taught. At least 2 data administrators will enter the information independently and proofread it. The electronic version of CRFs will be stored in the Third Affiliated Hospital of Zhejiang Chinese Medical University password-protected computer, which is available only to the investigator in charge of data management.

The Department of Science and Education in The Third Affiliated Hospital of Zhejiang Chinese Medical University, which is not participating in the study, will monitor the data, including the CRFs, protocol compliance, data management, treatment administration, and AEs.

The information of the grouping and the results of the study will be provided to the participants after the trial. Publications will only report aggregated data, and personal identities will not be disclosed.

### Date analysis

2.9

SPSS (version 21.0; SPSS Inc., Chicago, IL) will be used in statistical analyses by an independent statistician. Continuous variables will be presented as mean ± standard deviation, while categorical variables will be represented as percentages and numbers. The Chi-square test will be used to assess categorical variables, such as the characteristic and demographic data. The *t* test or Wilcoxon rank-sum test will be used for within- and inter-group comparisons according to the homogeneity and normality analysis. The date of the participant receiving at least one treatment will be included in the analysis. Missing data will be dealt with using the worst-case scenario method. We set the confidence interval to 95%. All tests are 2-tailed, and *P*-values <.05 will be considered to be significantly different.

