#### Primary process of recruitment

2.2.1

Participants will be recruited from the general population of Hangzhou Zhejiang. We will publicize the trial in multimodal strategies, including WeChat official accounts, newspapers, and recruitment posters at outpatient departments or inpatient wards.

The participants who are interested in the trial will contact us via WeChat or mobile phone. Informed consent must be obtained before the first interview. We will check if the participant meets the Rome IV Criteria and select the participant according to the inclusion and exclusion criteria. After the former procedure, the participant will enter the 2-week run-in period, during which the baseline information of the defecation will be collected, and the registered acupuncturist will teach the participants the location of the point and the details of the acupressure manipulation. The baseline assessment includes CBSMs, spontaneous bowel movements, the Bristol Stool Form Scale (BSFS),^[14,15]^ straining severity scores, and patient assessment of constipation quality of life (PAC-QOL).^[16]^ The study schedule is summarized in Table 1.

**Table 1 T1:** Schedule of recruitment, intervention, and assessments.

	Study period																		
TIMEPOINT	Interview	Baseline		Treatment								Follow-up							
Week		1	2	3	4	5	6	7	8	9	10	11	12	13	14	15	16	17	18
RECRUITMENT	×																		
Informed Consent	×																		
Eligibility Screen	×																		
Demography	×																		
Medical History	×																		
Randomization		×																	
INTERVENTIONS																			
Acupoint self-administered acupressure				×	×	×	×	×	×	×	×								
Sham acupoint self-administered acupressure				×	×	×	×	×	×	×	×								
ASSESSMENT																			
The proportion of participant whose CSBM≥3		×	×	×	×	×	×	×	×	×	×	×	×	×	×	×	×	×	×
SBM		×	×	×	×	×	×	×	×	×	×	×	×	×	×	×	×	×	×
BSFS		×	×	×	×	×	×	×	×	×	×	×	×	×	×	×	×	×	×
Straining severity scores		×	×	×	×	×	×	×	×	×	×	×	×	×	×	×	×	×	×
PAC-QOL				×			×				×				×				×
Medicine usage		×	×	×	×	×	×	×	×	×	×	×	×	×	×	×	×	×	×

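### Section 2.9 assigns the rank-sum test, which is for independent samples, to within-group comparisons, and names no between-group test that uses the baseline values of the secondary outcomes

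*Protocol article*

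**What the plan says.** Section 2.9 (Date analysis) has one sentence for continuous and ordinal outcomes. It offers a t test, of unstated type, or the rank-sum test: "Wilcoxon rank-sum test will be used for within- and inter-group comparisons according to the homogeneity and normality analysis". The signed-rank test is not named. For categorical data the section states: "The Chi-square test will be used to assess categorical variables, such as the characteristic and demographic data". The primary outcome, "the proportion of participants whose CSBM is ≥3 during weeks 3 to 10" (section 2.4.1), is binary and so falls under the chi-square sentence.

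Section 2.2.1 lists what is measured in the run-in: "The baseline assessment includes CBSMs, spontaneous bowel movements, the Bristol Stool Form Scale (BSFS"), followed by "straining severity scores, and patient assessment of constipation quality of life (PAC-QOL"). The secondary outcomes are then defined over later weeks. SBM, for example, is "bowel movements without using the medication for symptomatic relief of constipation during weeks 3 to 18" (section 2.4.2.1), and BSFS and straining have the same window. Section 2.4.2.5 adds: "The PAC-QOL will be assessed at weeks 2, 6, 10, 14, and 18". Section 2.9 names no test with a baseline term and does not say whether the two-sample tests act on post-treatment values or on changes.

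**The concern.** A within-group comparison here sets a participant's later values against the same participant's run-in values. The rank-sum test treats the two sets as coming from different people, so it ignores the correlation between them and uses too large a standard error. The non-parametric branch is likely to be used: straining is scored 0 to 3, BSFS has seven grades, and weekly SBM is a low count, so a normality check will often send these outcomes there.

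The second part concerns efficiency. The trial collects baseline values of its secondary outcomes, and the between-group tests named make no stated use of them. At stake are correct p-values for within-group change and precision in the randomised comparison of the secondary outcomes.

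**Working it through.** **Inputs from the protocol article.** 77 per group, 10% dropout, 80% power, two-sided 0.05 (sections 2.5 and 2.9). **Assumed, because the article gives no figure:** baseline-outcome correlation r = 0.3, 0.5 and 0.7; a within-group shift of 0.34 SD; normally distributed data.

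**The plan's own figure.** 69/(1 − 0.10) = 76.7, rounded up to 77 per group, or 154 in total. So 77 is consistent with about 69 evaluable per arm (77 × 0.90 = 69.3). The article gives no response rates, so 154 cannot be reproduced in full. It rests on the binary primary outcome and does not depend on this point.

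**Within-group comparison.** With equal variances, the paired difference in means has variance 2σ²(1 − r)/n, while an independent-samples test uses 2σ²/n. The standard error is overstated by 1/√(1 − r), which is 1.41 at r = 0.5. For a large-sample mean comparison, the true type I error is 2[1 − Φ(1.96/√(1 − r))]:

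- r = 0.3: 1.96/0.837 = 2.34, giving 1.9%
- r = 0.5: 1.96/0.707 = 2.77, giving 0.6%
- r = 0.7: 1.96/0.548 = 3.58, giving 0.03%

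Simulation of the rank-sum test itself on 69 pairs (20,000 runs; 4,000 for signed-rank) agrees closely:

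| r | Type I error, rank-sum | Type I error, signed-rank | Power, rank-sum | Power, signed-rank | Power, paired t |
|---|---|---|---|---|---|
| 0.3 | 0.020 | 0.049 | 0.49 | 0.64 | 0.65 |
| 0.5 | 0.006 | 0.054 | 0.48 | 0.77 | 0.79 |
| 0.7 | 0.001 | 0.051 | 0.49 | 0.94 | 0.95 |

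Power is at the 0.34 SD shift. The rank-sum test loses about 15, 29 and 45 percentage points against signed-rank. With 77 pairs, simulated type I error was 2.2% to 2.4%, 0.7% to 0.8% and 0.1% or less.

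**Between-group comparison, continuous secondary outcomes.** With 69 per arm, an unadjusted post-treatment comparison has 80% power for δ = (1.960 + 0.842) × √(2/69) = 0.477 SD. Adjusting for baseline multiplies the residual variance by 1 − r², so power is Φ(2.802/√(1 − r²) − 1.960):

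| r | 1 − r² | Power, ANCOVA | Per arm for 80% power | Power, change score |
|---|---|---|---|---|
| 0.3 | 0.91 | 0.84 | 63 | 0.66 |
| 0.5 | 0.75 | 0.90 | 52 | 0.80 |
| 0.7 | 0.51 | 0.98 | 36 | 0.95 |

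The per-arm figure is 69 × (1 − r²), rounded up. The change score has SD factor √(2(1 − r)) and is never better than ANCOVA in this table.

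**Primary outcome.** Chi-square was compared with logistic regression adjusted for baseline by simulation: 69 per arm, response about 39% against 18% (assumed), 1,500 runs per setting, so Monte Carlo error is about √(0.8 × 0.2/1500) = 1 point. By baseline effect in log-odds per SD, power was:

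- 0: 78.5% against 78.1%
- 0.3: 80.3% against 80.7%
- 0.6: 79.0% against 81.0%
- 1.2: 79.7% against 85.6%; another run gave 78.4% against 83.9%

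The gain is about 0 to 2 points unless baseline is very strongly prognostic.

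**Is there a usable baseline?** Table 1 marks randomisation in week 1 of the run-in, and section 2.3 places the acupressure teaching after randomisation and within the run-in. The run-in values may therefore be recorded after allocation. The first PAC-QOL is at week 2 in section 2.4.2.5, but Table 1, as its columns read in the extracted text, marks it at week 3, when treatment starts.

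**The case against.** The strongest reply is that the wording error is narrow and harmless to the main conclusion. Much of this stands.

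- A reader might infer that every within-group test is wrong. The article does not support that: the t test is not called independent and may be paired. The error is certain only for the rank-sum test.
- A reader might fear false positive within-group claims. With positive correlation the error runs the other way: it loses power. Within-group tests also do not compare acupoint with sham.
- A reader might say that the plan ignores baseline. The article does not say so. Within-group comparisons presumably use the run-in data, the two-sample tests could be applied to change scores, and an adjusted model may stand in an analysis plan that is not shown. Unadjusted tests between randomised arms are valid, so the cost is precision, not bias.
- A reader might infer that each week is tested separately. Section 2.9 does not state this, and weekly values may be averaged over a period. Choosing between t and rank-sum after a normality check is not ideal, but it is a stated rule and common practice. Neither is an error in this document.
- A reader might extend the gain from adjustment to the primary outcome. That gain depends on a strong baseline effect. The Introduction defines severe chronic constipation by fewer than 3 CSBM per week, which narrows the range of baseline CSBM and makes such an effect doubtful.

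What the reply does not remove is that section 2.9 positively assigns an independent-samples test to paired data. That is a misstatement, not a detail deferred to another document.

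**Conclusion.** The point holds in limited form. The rank-sum test is the wrong test for within-group change: type I error is about 2%, 0.7% and 0.1% instead of 5% at assumed correlations of 0.3, 0.5 and 0.7, with a matching loss of power. The direction holds for any positive correlation. The exact values rest on simulated normal data and are indicative for ordinal scores with ties.

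Baseline adjustment of SBM, BSFS, straining and PAC-QOL is a recommended improvement and not the correction of an error. At the same assumed correlations it raises power from 0.80 to about 0.84, 0.90 and 0.98, provided that the baseline is a true one.

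The chi-square primary analysis and the total of 154 stand. Any gain from adjusting the primary outcome for baseline CSBM is uncertain and may be small. Severity is moderate to minor; the documents do not support treating this as a defect that must be repaired before the trial can be relied on.

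**What to change.** In section 2.9:

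1. For within-group change, name the paired t test or the Wilcoxon signed-rank test, and label these results descriptive. Keep the rank-sum test and the independent t test for between-group comparisons only.
2. For SBM, BSFS, straining and PAC-QOL, add a between-group ANCOVA, or a mixed model for the repeated values, with the participant's baseline value as covariate. The choice of period or time point can be left to the analysis plan.
3. Before adjusting, reconcile the baseline timing: state whether the run-in values precede randomisation (Table 1, sections 2.2.1 and 2.3), and whether the first PAC-QOL is at week 2 (section 2.4.2.5) or week 3 (Table 1). A value taken after allocation or after treatment has started should not serve as the baseline covariate.

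The cost is a few sentences, agreed before unblinding, and a little more analysis work. The methods are available in the stated software. No extra data, participants or change to the primary analysis are needed.

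### For continuous secondary outcomes a check on the trial data chooses between t test and rank-sum test, yet means are always reported, so the P-value may not address the reported difference

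*Protocol article*

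**What the plan says.** Section 2.9 (Date analysis) of the protocol article sets one rule for continuous data: a t test or a rank-sum test, for within-group and between-group "comparisons according to the homogeneity and normality analysis". The same paragraph fixes the summary whichever test is used: "Continuous variables will be presented as mean ± standard deviation". Tests are two-sided at 0.05, and 95% confidence intervals are promised. Categorical variables get a chi-square test.

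The section does not say which result of the check leads to which test. The natural reading is a t test if the data look normal with equal variances, and otherwise the rank-sum test. It also does not say whether the aim is to compare means or whole distributions.

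The rule reaches the secondary outcomes in section 2.4.2 that are counts or scores: SBM, stool form, straining (0-3), PAC-QOL and weekly frequency of rescue use. It does not reach the primary outcome in section 2.4.1 ("The primary outcome of this trial is the proportion of participants whose CSBM is ≥3 during weeks 3 to 10") or the matching weeks 11-18 outcome in section 2.4.2.2, because both are proportions.

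**The concern.** The t test compares means. The rank-sum test asks whether values in one arm tend to exceed those in the other. It can be read as a comparison of averages only if the two distributions have the same shape. Under section 2.9 the data decide which question is answered, while the summary shown beside the P-value is always a mean. The P-value and the reported difference can then disagree, and a reader cannot tell beforehand which hypothesis will be tested.

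Bowel-movement counts and rescue use are likely to be skewed, so the mismatch would be the ordinary case for them. Naming homogeneity as a criterion does not help, because the rank-sum test is not a remedy for unequal variances. At stake is the interpretation of the continuous secondary results, not the primary conclusion.

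**Working it through.** **Inputs from the protocol.** Section 2.5: "Considering a 10% dropout rate, we need 154 subjects in total and 77 subjects per group". Evaluable per arm: 77 × 0.90 = 69.3, so about 69; conversely 69 / 0.90 = 76.7, rounded up to 77. Allocation is 1:1 and alpha is 0.05 two-sided.

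**No plan figure to reproduce.** The protocol gives no SD, shape or variance ratio for any continuous outcome and no error rate for the rule. All distributions below are assumptions.

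**Rule simulated.** Shapiro-Wilk in each arm and Levene's test, each at 5%; pooled t test if all pass, otherwise rank-sum. True means are equal in both arms. There were 3,000 to 6,000 runs per scenario. The Monte Carlo standard error at 5% with 4,000 runs is √(0.05 × 0.95 / 4000) = 0.0034, or about 0.3 percentage points.

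**Step 1: weekly counts.** Negative binomial, mean 3, variance = m + m²/k:
- k = 50: 3 + 9/50 = 3.18, SD 1.8
- k = 3: 3 + 9/3 = 6, SD 2.4
- k = 1.5: 3 + 9/1.5 = 9, SD 3.0

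Results from repeated runs with 69 or 70 per arm:

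| SDs | Rule | Welch |
|---|---|---|
| 1.8 vs 2.4 | 10.3-11.4% | 4.5-5.3% |
| 1.8 vs 3.0 | 23.6-24.0% | 5.5% |
| equal | 4.4-5.2% | 4.3-5.2% |

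In the unequal-spread count scenarios normality failed in every run and homogeneity alone decided the route in none. The rule rejected exactly as often as a rank-sum test fixed in advance.

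**Step 2: other shapes, 69 per arm.**

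| Shape | SDs | Rule | Welch |
|---|---|---|---|
| Normal | ratio 1 | 5.1% | 5.1% |
| Normal | ratio 1.5 | 4.7% | 4.3% |
| Normal | ratio 2 | 5.9% | 4.9% |
| Normal | ratio 3 | 6.6% | 5.1% |
| Symmetric 0-4 score, mean 2 | 0.5 vs 1.0 | 6.1% | 5.2% |
| Skewed 0-4 score, mean 1.2 | 0.5 vs 0.75 | 9.1% | 4.8% |
| Skewed 0-4 score, mean 1.2 | 0.5 vs 1.0 | 23.4% | 5.6% |
| Gamma, mean 3 | 1.5 vs 1.5 | 4.7% | 4.8% |
| Gamma, mean 3 | 1.5 vs 1.8 | 7.2% | 5.0% |
| Gamma, mean 3 | 1.5 vs 2.25 | 15.8% | 5.2% |
| Gamma, mean 3 | 2 vs 3 | 24.4% | 4.9% |
| Gamma, mean 3 | 1.5 vs 3 | 45.0% | 5.7% |
| Gamma, mean 3 | 1.5 vs 4.5 | 91.2% | 6.5% |
| Lognormal, mean 3 | 1.5 vs 2.25 | 20.0% | 5.4% |

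With 77 per arm the rates are similar or slightly higher (gamma 2 vs 3: 28.4%).

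**Step 3: outcomes closer to the protocol's own.** Rescue-use counts with mean 0.7 and unequal dispersion gave 13.8% (Welch 5.5%). Eight-week mean SBM with between-person SDs of 1 vs 1.5, 1 vs 2 and 1.5 vs 2 gave 7.8%, 20.0% and 8.7% (Welch 5.3-5.8%). With equal between-person SD of 1, these averages passed the check in about 21% of runs, so the choice of test was left to chance.

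**Reading.** Excess rejection of equal means needs skew and unequal spread together. Either alone gives about 5-7%.

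**The case against.** The strongest reply is that nothing is wrong with the rank-sum test on its own terms. Wherever the rate exceeded 5%, the two distributions did differ, so a rejection is not a type I error for the rank-sum null hypothesis. If acupressure has no effect and the distributions are identical, the rule stays near 5%. This stands. The rates above are errors only if the P-value is read as evidence about means, which reporting means invites.

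A reader might infer that the pre-test itself, or the routing of unequal-variance data to the rank-sum test, inflates the error rate to 11-24%. That is not supported. In the counts giving those figures, normality alone sent every dataset to the rank-sum test. With normal data and SD ratios of 1.5-2, where Levene's test mostly decided the route, the rule rejected about 5-6%.

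Equal means with unequal spread is also a special case. If only some participants respond and none worsen, the means differ as well. The simulation therefore shows what the test addresses; it does not predict this trial's error rate.

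The routing is inferred. Homogeneity might mean only the choice between the pooled and unequal-variance t test. Skewed outcomes would still go to the rank-sum test on normality.

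A condensed article may leave the test for each outcome to an analysis plan. Here, however, the article states a rule, and the point concerns that rule. That one outcome would be tested differently from week to week is a further inference: section 2.9 does not say that tests are run weekly.

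**Conclusion.** The point holds in a limited form. Section 2.9 lets the trial data choose between a test of means and a rank test while always reporting means, so for skewed continuous secondary outcomes the P-value need not address the reported difference.

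The size depends wholly on assumed skew and spread: about 7% to over 45% rejection of equal means when both are present, and 10-24% for the simulated counts. No single rate can be attributed to this plan, because the protocol gives no SDs or shapes. The primary outcome and the weeks 11-18 proportion are untouched. The change is worth making because it is cheap and aligns the P-value, estimate and interval; the trial's main conclusion does not depend on it.

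**What to change.** In section 2.9, delete the choice by normality and homogeneity. For SBM, rescue frequency and PAC-QOL, name in advance one between-group comparison of means that does not assume equal variances (a Welch t test, or a linear model with robust standard errors), and report the mean difference with its 95% CI. Keep the rank-sum test as a labelled sensitivity analysis, or as the fixed choice for the 0-3 straining score.

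The cost is one sentence; no new data are needed and Welch is available in SPSS. At 1:1 allocation a fixed pooled t test did almost as well (4.3-6.7% in the equal-mean runs), so fixing a comparison of means matters more than which version is used. The downside is that Welch can lose some power to the rank-sum test if data are heavy-tailed. In the alternatives that were run its power was equal or better (79% against 63% in one assumed case where 30% of one arm respond), but that too depends on the assumptions.
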